### Standardised evaluation protocol

2.5

A common evaluation protocol has been developed within the project to ensure methodological consistency and enable meaningful cross-site comparisons (see Table 3 for details on self-administered questionnaires). This standardised approach allows for the integration of data from diverse pilot sites while preserving inter-comparability and scientific rigor.

**Table 3 T3:** Self-administered questionnaires of COMFORTage-Ace (basal, one-year and two-year follow-up).

Category	Measurement Tool/Description
Quality of life	QoL-AD (85)
Depression	HADS (82)
	Geriatric Depression Scale (86)
Sleep quality	Pittsburgh Sleep Quality Index (PSQI) (87)
Satisfaction with intervention	Questionnaire for User Interaction Satisfaction (QUIS) (88)
Alcohol consumption	Alcohol Use Disorders Identification Test (AUDIT) (89)
Social isolation	UCLA Loneliness Scale (90)
IADL	Lawton IADL scale (84)
Daily living activities	ADL (83)
Physical activity	International physical activity questionnaire (IPAQ) (91)
Nutritional assessment	Mini Nutritional Assessment (MNA) (92)

QoL-AD, quality of life in alzheimer's disease; HADS, hospital anxiety and depression scale; IADL, instrumental activities of daily living; ADL, activities of daily living.

The collection of genetic data, CSF and plasma samples, as well as MRI scans, is carried out in strict adherence to bioethics committee–approved protocols and in compliance with relevant national and international regulations, including the GDPR. Blood samples are obtained by licenced nurses in a designated clinical area, and CSF procedures are performed by a neurologist or anesthesiologist at Ace. Prior to any procedure, participants receive detailed information and are given sufficient time to ask questions, ensuring informed understanding and comfort.

Given the cognitive challenges faced by many participants, the completion of questionnaires is designed to be flexible: participants are allowed several days and may receive support from trained staff as needed. To minimize any perception of coercion and uphold ethical standards, the Participant Information Sheet explicitly states that participation is voluntary and that individuals may withdraw at any time without consequences to their clinical care. Furthermore, it is made clear that the clinical procedures performed in the context of the project are independent of the study's research objectives. This ensures full respect for participant autonomy and safeguards their rights throughout the research process.

### Intervention plan

2.6

The active group (*n* = 50) will participate in in-person visits, using the cognitive and functional stimulation tools developed by the Consortium and completing follow-up assessments when needed. Sessions will be conducted by a neuropsychologist and delivered twice per week in one-hour format, ensuring sufficient intensity and structure to promote cognitive engagement. Participants will attend these sessions in small groups of approximately five to seven participants, allowing the neuropsychologist to combine individualised attention with the therapeutic benefits of group interaction. The content for each participant will be customised by combining recommendations from the VHP and input from the neuropsychologist conducting the sessions, who will direct the session intervention. The sessions will take place at Ace's facilities, ensuring a controlled and supportive environment tailored to participants’ needs. This structured schedule provides a consistent therapeutic framework during the first year of follow-up. Importantly, needed medication regimens will be maintained throughout the intervention, ensuring no disruption of clinical care.

The protocol will integrate individualised and group-based approaches, with activities tailored to each participant's functional abilities and progress. For participants with lower digital literacy, face-to-face support will play a pivotal role, ensuring comprehension and fostering a confident and engaging experience. Participants demonstrating sufficient motivation and engagement may have the option to continue activities at home, supported by direct and remote monitoring from assigned professionals. This ensures consistent guidance and task adaptation based on evolving needs. The digital tools will provide multiple outputs (*i.e.*, dosage, time of exposure, performance metrics) which will be analysed during and after the intervention. These outputs will serve a dual purpose: enhancing the dynamic functionality of the VHP and providing critical data to evaluate the intervention's efficacy within this study.

In the Pilot 3 study, the tools used to achieve the functional stimulation targets were carefully selected by the researchers at Ace. They evaluated different options provided by the consortium's technology partners to identify those best suited to the specific needs and characteristics of their participants with cognitive decline. Designed for use by both participants and professionals, these tools facilitate seamless data integration and effectively support the program's goals. The tools used in this pilot study include:
Healthentia (46). Healthentia is a class IIa medical device, intended for supporting subject telemonitoring, decision-making and virtual coaching (47, 48). The collection of physiological data includes heart rate, blood pressure, oxygen saturation, and weight, directly transmitted to care providers via automated electronic means in combination with validated internet of things devices (when available for other clinical partners, not for our pilot). The information collected is further enriched with the transmission of patient's outcomes and outcome scores related to patient's health status, health-affecting factors, health-related quality of life, disease knowledge and adherence to treatment, through validated questionnaires. Participants capable of remotely interacting with the tool beyond face-to-face sessions tend to report more frequently, contributing regular (daily or weekly) data that can inform timely care plan adjustments. All these parameters are visualised (subjects-based dashboards) and mathematically treated (trends analysis, alerts) for supporting experts’ decision-making procedures.Eligence (49). Eligence is an online platform designed for brain training through interactive games, created by specialists in neuropsychology aimed at individuals in the early stages of dementia, for rehabilitation and prevention of cognitive decline. It features 40+ games and activities that exercise the basic cognitive skills such as memory, reasoning, attention, orientation, executive functions, construction skills, language. Through Eligence, healthcare professionals can create personalised training sessions for individuals and groups, monitor performance in real-time and easily generate detailed evaluation reports. It is accessible from anywhere and any device with an internet connection.Linguistic Games (50). A novel cognitive and linguistic tool has been designed upon the main objective to exploit multiple cognitive processes that are involved in language performance and speech production and comprehension. The initial functionality of the mock-up tool was in 2D, but also some subtasks have been designed in 3D to introduce higher cognitive-processing demands; however, the tool is not intended as different versions for separate groups but rather as graded levels of difficulty applicable across healthy adults, adults with subjective cognitive decline, and those with mild cognitive impairment. These novel linguistic tests can assess different cognitive abilities through the vehicle of language competence such as attention, memory, language, psychomotor abilities, processing speed and executive functions. The linguistic mock-up has been designed based on Usability and Accessibility Guidelines (51–55), while realistic contexts from older adults’ daily routines have been incorporated for example tasks based on vocabulary or short scenarios related to household chores, daily mobility, travel planning or participation in social events (56).The data generated by these three digital tools, as well as the clinical, neuropsychological, or biological data relevant to the project—whether retrospective (historical data from Ace) or prospective (related to the follow-up of the two study groups)—will be shared with the Consortium using the VHP. These multimodal data will feed into the platform and serve as input for AI algorithms and PDTs, which aim to predict individual health trajectories and propose tailored interventions. This process exemplifies the integration of digital tools, clinical knowledge, and computational models into a unified, adaptive care system. Audio recordings from the spontaneous speech protocol will not be shared for confidentiality reasons.

The active group will complete the cognitive and functional stimulation intervention at the one-year follow-up. In parallel, the control group will follow the same assessment protocol as the active group, ensuring consistency and comparability in the assessment process. However, participants in the control group will not participate in the stimulation activities provided through the digital platforms developed by the project.

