### Study participants

2.3

The study participants for the Ace Pilot will consist of 100 individuals aged 60–85, divided into two groups of 50 participants each (active and control groups), see Figure 1. Eligible participants will be diagnosed with MCI according to Petersen criteria (13, 28) with a Clinical Dementia Rating (CDR) score of 0.5 (29) or mild AD dementia as defined by the National Institute on Aging-Alzheimer's Association (NIA-AA) criteria (30) with a CDR score of 1 (29).

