**Figure 1 F1:**

Study design and participant flow for pilot 3 at Ace.

Participants will follow a standardised protocol, with a consensus diagnosis determined by the research team based on a comprehensive evaluation, including neurological, neuropsychological, and social assessments (31). Additionally, participants must show proficiency in using digital devices such as mobile apps, tablets, or computers, as these tools are essential for both the intervention and monitoring processes.

The sample size was defined based on feasibility considerations, reflecting the expected number of eligible individuals who can be recruited during the study period. This estimate considers the typical annual flow of newly assessed patients who undergo the full diagnostic protocol, including neuropsychological evaluation, CSF and MRI, and who are able to attend regular on-site sessions at the centre. As a result, the target of 100 participants represents a realistic and achievable recruitment goal within the operational context of the Memory Unit.

In accordance with Spain's Data Protection Law (Organic Law 3/2018), all participants were informed by a neurologist about the study's goals and procedures before signing an informed consent form. Patient privacy and data confidentiality were safeguarded in compliance with applicable regulations.

Exclusion criteria include a history of medical conditions that could confound cognitive assessments or hinder participation, such as traumatic brain injury, severe depression, stroke, or brain tumors. Participants with significant uncorrected visual or auditory abnormalities, those without access to a digital device or internet connection, and individuals unable to attend regular in-person sessions at Ace will also be excluded.

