### Analysis plan

2.7

The primary objective of Pilot 3 is to compare cognitive decline between the active and control groups after a two-year follow-up period. The neuropsychological structure underlying the primary outcome has been previously defined and validated by an expert panel of neuropsychologists (26, 27). Based on this structure, five composite scores will be derived using Structural Equation Modelling, following the methodology described in (23). To evaluate the impact of the intervention across two conditions on these neuropsychological composites, mixed models will be employed. These models will include three time points (baseline, one-year follow-up and two-year follow-up) and will also be applied to secondary outcome measures, such as quality of life, physical activity, and satisfaction with the intervention. Alterations in plasma biomarkers, including pTau181 and pTau217, will adhere to the same analytical framework, allowing for a comprehensive evaluation of both cognitive and biological markers.

In addition, the study will explore modulating effects, such as biological factors (AD-related biomarkers in CSF, PRS, *APOE*, MRI parameters, plasma biomarkers, comorbidities, and medication use) through interaction analyses within the mixed models. Associations between spontaneous speech measures, neuropsychological composites, and plasma biomarkers will be examined using regression models and advanced machine learning techniques. This aspect of the study aims to identify the most predictive parameters of pre- and post-intervention slopes across the five neuropsychological composites. By leveraging these predictive models, the study seeks to advance the understanding of how specific variables contribute to cognitive decline and its modulation, ultimately informing precision medicine approaches for dementia care.

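### Stimulation is delivered in session groups in the active arm only, but the mixed models described in section 2.7 make no provision for session group; if outcomes correlate within groups, standard errors will be too small

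*Protocol article*

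**What the plan says.** Section 2.3 plans 100 participants, 50 per arm, and says of this number: "The sample size was defined based on feasibility considerations".

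Section 2.6 sets out delivery in the active arm: "Sessions will be conducted by a neuropsychologist and delivered twice per week in one-hour format". It continues: "Participants will attend these sessions in small groups of approximately five to seven participants". The stated purpose of this format is to "combine individualised attention with the therapeutic benefits of group interaction". The same section also individualises the programme: "The content for each participant will be customised by combining recommendations from the VHP and input from the neuropsychologist conducting the sessions". Sessions run during the first year. Controls follow the same assessments but take no part in the stimulation activities.

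Section 2.7 gives the analysis: "To evaluate the impact of the intervention across two conditions on these neuropsychological composites, mixed models will be employed". The models use baseline, year 1 and year 2, and are extended to the secondary outcomes and plasma biomarkers. The section lists biological and clinical effect modifiers. Session group and session leader are not mentioned, and no random-effects or covariance structure is given.

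**The concern.** Participants are randomised individually, but one arm is then treated in groups. This is a partially nested design. The article itself supplies a reason for correlation within groups, since it lists "the therapeutic benefits of group interaction" among the aims of the format, and its Discussion names social interaction as one possible source of improvement. If peers or leader affect the outcome, two people from the same session group resemble each other more than two people from different groups, and the active-arm mean varies more than 50 independent observations would suggest.

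A model built only from arm, visit and repeated measures within person misses that extra variance. Intervals for the active-control contrasts would then be too narrow, on the five composites and on secondary outcomes such as quality of life. Part of the remedy is also time-critical. The model can be settled later, but group membership has to be captured while the sessions run.

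**Working it through.** The article states no power, alpha, effect size, SD or ICC, so there is no figure of its own to reproduce. The check asks how far an analysis that leaves out session group would be off.

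**Inputs from the article**
- 50 participants per arm (section 2.3).
- Session groups of m = 5 to 7 in the active arm, none in the control arm (section 2.6). Number of groups: 50/7 = 7.1 to 50/5 = 10.

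**Assumptions**
- Two-sided alpha 0.05, equal total variance in the two arms, no dropout.
- ICC within session groups of 0, 0.01, 0.05 or 0.10, for the quantity compared between arms.

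**Formulas**
- Active-arm design effect: DE = 1 + (m - 1) × ICC.
- True SE divided by the SE under independence: R = sqrt((DE + 1)/2). Only one of two equal arms is inflated.
- Actual type I error: 2 × (1 - Φ(1.96/R)).
- Effective active-arm size: 50/DE.

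**Example**, m = 6 and ICC 0.05: DE = 1 + 5 × 0.05 = 1.25; R = sqrt(2.25/2) = 1.061; 1.96/1.061 = 1.848; type I error 0.065; effective size 50/1.25 = 40.

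| ICC | m | DE | R | Effective n (active) | Type I error | Simulated |
|---|---|---|---|---|---|---|
| 0 | 5-7 | 1.00 | 1.000 | 50 | 0.050 | 0.049-0.051 |
| 0.01 | 5 | 1.04 | 1.010 | 48.1 | 0.052 | 0.050 |
| 0.01 | 6 | 1.05 | 1.012 | 47.6 | 0.053 | 0.053 |
| 0.01 | 7 | 1.06 | 1.015 | 47.2 | 0.054 | 0.051 |
| 0.05 | 5 | 1.20 | 1.049 | 41.7 | 0.062 | 0.060 |
| 0.05 | 6 | 1.25 | 1.061 | 40.0 | 0.065 | 0.065 |
| 0.05 | 7 | 1.30 | 1.072 | 38.5 | 0.068 | 0.070 |
| 0.10 | 5 | 1.40 | 1.095 | 35.7 | 0.074 | 0.073 |
| 0.10 | 6 | 1.50 | 1.118 | 33.3 | 0.080 | 0.080 |
| 0.10 | 7 | 1.60 | 1.140 | 31.2 | 0.086 | 0.087 |

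The last column comes from 40,000 simulated trials per row, with 10 groups of 5, 8 groups of 6 or 7, or 7 groups of about 7, against 50 unclustered controls. Each trial was analysed by a two-sample t-test that ignores group. This is simpler than a three-visit mixed model, but it isolates the same omission.

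**Precision once clustering is allowed for.** Under independence, the difference detectable with an assumed 80% power is (1.96 + 0.84) × sqrt(2/50) = 0.56 SD. Multiplied by R, this becomes 0.59-0.60 SD at ICC 0.05 and 0.61-0.64 SD at ICC 0.10.

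**The case against.** The strongest objection is that a reader might infer from section 2.7 that all participants are treated as independent, and the article does not say that. It gives no random effects at all, and a condensed article may leave these to a full protocol or SAP that is not shown. This stands. The point is limited to what is described: two conditions, three time points and no provision for session group.

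A reader might also infer that group members share leader, content and peers for a whole year. The text does not support this. Content is customised for each participant, the number of neuropsychologists is not given, and nothing says that group membership stays fixed. If one person leads every group, leader adds no variance between groups.

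Third, the harm depends on an ICC that nobody has stated. At 0.01 it is negligible. The primary comparison is at year 2, a year after sessions end, and any correlation may have faded by then. It is therefore not established that error exceeds its nominal level for every outcome.

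Fourth, with individual randomisation, if the intervention affects nobody, placing active participants into session groups afterwards does not inflate the variance of the arm mean, and the test keeps its size. The type I figures apply where group-specific effects exist but average to zero. Where the intervention does have effects that vary by group, the fault shows as intervals that are too narrow.

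Finally, nothing suggests that membership will go unrecorded. Sessions are scheduled, staffed and held on site. Still, the article's listed tool outputs and assessment tables do not name group or leader.

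These objections limit the size and certainty of the problem. They do not remove it: delivery is nested in one arm, the described model omits it, and the direction of the error is known whenever the ICC is positive.

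**Conclusion.** The point holds conditionally. The active arm alone is treated in about 7 to 10 session groups, with group interaction named as therapeutic, and the analysis as described makes no provision for this. Followed as described, it understates the uncertainty of the active-control contrasts if outcomes correlate within groups. The effect ranges from none at ICC 0, through negligible at 0.01 and modest at 0.05, to a type I error of at most about 8.6% at 0.10 with groups of seven. These figures rest on the assumed ICC range, equal total variance, no dropout and two-sided alpha 0.05.

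Because the sample size rests on feasibility, no stated power figure is overturned. The documents do not support saying that the planned models assume independence, or that the tests are certainly too liberal.

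**What to change.** - During year 1, record the session group and session leader of each active participant, including any change of group.
- Add to section 2.7 a partially nested mixed model: a random session-group effect in the active arm at post-baseline visits, controls treated as singletons, and Satterthwaite or Kenward-Roger degrees of freedom because there are only about 7 to 10 groups. Apply it to all active-control contrasts.
- If the group variance cannot be estimated with so few groups, report a sensitivity analysis over a stated ICC range.
- If a single neuropsychologist leads every group, state that the leader's effect cannot be separated from that of the intervention.

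The cost is a small addition to data capture (group and leader), one random effect and slightly wider confidence intervals. If the full protocol or SAP already contains such a term, one sentence in section 2.7 saying so, with confirmation that membership is recorded, is enough.

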### Analysis plan

2.7

The primary objective of Pilot 3 is to compare cognitive decline between the active and control groups after a two-year follow-up period. The neuropsychological structure underlying the primary outcome has been previously defined and validated by an expert panel of neuropsychologists (26, 27). Based on this structure, five composite scores will be derived using Structural Equation Modelling, following the methodology described in (23). To evaluate the impact of the intervention across two conditions on these neuropsychological composites, mixed models will be employed. These models will include three time points (baseline, one-year follow-up and two-year follow-up) and will also be applied to secondary outcome measures, such as quality of life, physical activity, and satisfaction with the intervention. Alterations in plasma biomarkers, including pTau181 and pTau217, will adhere to the same analytical framework, allowing for a comprehensive evaluation of both cognitive and biological markers.

In addition, the study will explore modulating effects, such as biological factors (AD-related biomarkers in CSF, PRS, *APOE*, MRI parameters, plasma biomarkers, comorbidities, and medication use) through interaction analyses within the mixed models. Associations between spontaneous speech measures, neuropsychological composites, and plasma biomarkers will be examined using regression models and advanced machine learning techniques. This aspect of the study aims to identify the most predictive parameters of pre- and post-intervention slopes across the five neuropsychological composites. By leveraging these predictive models, the study seeks to advance the understanding of how specific variables contribute to cognitive decline and its modulation, ultimately informing precision medicine approaches for dementia care.

Building upon this analytical framework, a comprehensive ML approach will be integrated to enhance predictive modelling and improve the understanding of cognitive decline in response to intervention. In contrast to earlier work that relied primarily on shallow or ensemble learning methods applied to acoustic features, the present study will evaluate a broader range of modelling strategies. Acoustic, prosodic, and temporal speech features will be analysed alongside linguistic features derived from automatic transcription, including lexical, semantic, syntactic, fluency-related, and sentiment-related measures (57). Deep-learning architectures—such as convolutional neural networks and autoencoder-based models—will be explored for both acoustic representations and linguistic embeddings. The potential use of large language models (LLMs) will also be examined to extract contextual and semantic information from transcripts (58).

To manage the complexity of high-dimensional data, feature engineering and dimensionality reduction techniques will be applied. Specifically, wrapper-based feature selection methods and autoencoders will be tested to extract the most relevant predictors while minimizing redundancy and noise. A regression-based predictive framework will be used to evaluate the contribution of cognitive, biological, and speech-derived parameters, incorporating ensemble methods such as Random Forests and Gradient Boosting.

To improve model interpretability, explainable AI techniques, such as SHapley Additive exPlanations (SHAP) (59), will be employed to identify the key factors driving cognitive outcomes. Furthermore, longitudinal analyses will be conducted to track cognitive changes over time, enabling an assessment of individual responses to interventions and facilitating the early identification of cognitive decline. This machine learning-driven approach is expected to complement traditional statistical methods, enhancing both the accuracy and interpretability of predictive models in the context of dementia research.

In addition to these methodological goals, the study will also assess how the integration of digital health tools within the VHP supports clinicians in decision-making processes. The increased frequency, granularity, and clarity of data provided by these tools are expected to improve clinical insight, facilitate earlier detection of cognitive decline, and enable more timely and personalised interventions, thereby reinforcing trust in AI-assisted models as complementary assets in routine care.

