### Study design

2.1

The Ace Pilot (Pilot 3) is a randomised, open-label, two-year clinical trial comparing outcomes between an active group receiving a structured cognitive and functional stimulation program and a control group receiving standard care. In parallel, retrospective datasets from Ace's existing cohorts, including clinical, neuropsychological, genetic, CSF and plasma biomarkers, and MRI data, will be shared with the consortium to support the development and validation of the VHP's AI algorithms.

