### Scheduled visits and assessments

2.4

Participants will be prospectively recruited at Ace's Memory Unit. The majority of patients in this unit are beneficiaries of the Catalan public health system and are typically referred by their general practitioners. Both the active and control groups will follow identical evaluation procedures, as outlined in Table 1, ensuring consistency and comparability in data collection and assessment across the study population.

**Table 1 T1:** Overview of scheduled visits and assessments in pilot 3.

Evaluation/sample		Pre-intervention	Follow-up year 1	Follow-up year 2
Neurology		✓	✓	✓
Neuropsychology		✓	✓	✓
Nursing		✓	✓	✓
Spontaneous speech		✓^a^	✓^a^	✓^a^
MRI		✓	✕	✕
Fluid biomarkers	Plasma	✓	✓	✓
	CSF	✓	✕	✕
	Saliva	✓	✕	✕
Genotyping (PRS and *APOE* ɛ4)		✓	✕	✕
Cognitive and functional stimulation activity		✕	✓^b^	✕
Self-reported data		✓	✓	✓

MRI, magnetic resonance imaging; CSF, cerebrospinal fluid; PRS: Polygenic Risk Score.

^a^
Every 3–4 months remotely.

^b^
Weekly during the first year of follow-up, done remotely and in person.

Clinical, neuropsychological, and biological data will be systematically collected throughout the study to provide a comprehensive evaluation of participants’ progress and the intervention's impact. Clinical and neuropsychological assessments will be conducted in a face-to-face setting at the three critical time points: baseline (pre-intervention) and one-year and two-year follow-ups. These assessments will yield essential insights into participants’ cognitive and functional status over time, enabling a detailed analysis of the intervention's efficacy. Additionally, self-reported data will be gathered via standardised questionnaires during participants’ regular visits as part of the intervention activities. These face-to-face sessions will be carried out during the first year of the project, allowing consistent monitoring of clinical conditions, neuropsychological performances, and subjective experiences, such as quality of life and activity levels. The second-year follow-up is designed to extend the monitoring period and assess the sustainability of the intervention's effects after its conclusion, providing relevant insights into medium-term outcomes. At this final stage, the same clinical, neuropsychological, and self-reported measures are reassessed.

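### Satisfaction with the intervention is assigned to a two-arm, three-visit mixed model, although controls never receive the intervention and nobody has received it at baseline

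*Protocol article*

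**What the plan says.** Section 2.7 (Analysis plan) introduces the main model: "To evaluate the impact of the intervention across two conditions on these neuropsychological composites, mixed models will be employed". It gives these models three time points (baseline, year 1 and year 2) and extends them: they "will also be applied to secondary outcome measures, such as quality of life, physical activity, and satisfaction with the intervention". Satisfaction is thus named in the list of outcomes for this model, beside two outcomes that everyone can report at any visit.

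Table 3 in section 2.5 measures satisfaction with the intervention by the QUIS. The table is captioned "Self-administered questionnaires of COMFORTage-Ace (basal, one-year and two-year follow-up" and makes no exception for the QUIS row. Section 2.4 says of the assessments: "Both the active and control groups will follow identical evaluation procedures, as outlined in Table 1". Section 2.6 repeats that controls follow the assessment protocol of the active group.

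On exposure, section 2.1 describes "a control group receiving standard care", and section 2.6 states that "participants in the control group will not participate in the stimulation activities provided through the digital platforms developed by the project". Section 2.4 labels the baseline visit as pre-intervention. Table 1 and section 2.6 confine the stimulation programme to the first year, ending at the one-year visit.

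**The concern.** An outcome that asks how satisfied someone is with an intervention has a value only for people who have received it. The model in section 2.7 needs a value in both arms and at a visit before exposure. Followed as written, the rule has two possible results. If controls and baseline respondents do fill in the QUIS, the software will return a group effect and a group-by-time effect, but those coefficients will set ratings of the intervention against answers about something the respondent has not experienced. If they do not fill it in, the model cannot be fitted as described. Either way, a named secondary outcome has no interpretable result under its stated analysis. In the first case, a number without meaning could be reported beside valid ones for quality of life and physical activity.

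**Working it through.** The plan gives no figure to reproduce on this point. The total of 100 is a feasibility target (section 2.3), and the only arithmetic to confirm is 50 + 50 = 100. The check asks which terms of the stated model can be defined.

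**Inputs**
- Two arms of 50 (section 2.3).
- Three visits: baseline, year 1 and year 2 (section 2.7, Table 3).
- The intervention is given to the active arm only, after baseline, and ends at year 1 (sections 2.4 and 2.6, Table 1).

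**Step 1: who has something to rate**

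| Arm | Baseline | Year 1 | Year 2 |
|---|---|---|---|
| Active | no, not yet exposed | yes, at end of programme | yes, by recall a year after it ended |
| Control | no | no | no |

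Two of the six cells have an intervention to rate.

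**Step 2: what the model can estimate**

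The article does not write the model out. I assume the usual fixed-effects layout: an intercept, arm, two visit terms and two arm-by-visit terms, making 1 + 1 + 2 + 2 = 6 parameters.
- With all six cells filled, the design matrix has rank 6 and every term is estimable.
- With only the two exposed cells, it has rank 2. The arm term, both visit terms and both arm-by-visit terms are not estimable. The contrast that remains is year 2 minus year 1 within the active arm.
- With all three active-arm cells and no controls, it has rank 3. The arm and arm-by-visit terms are still not estimable, and the added baseline cell holds no rating of the intervention.

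**Step 3: how many records could be affected**

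This is an upper bound. It assumes that every participant in both arms completes the QUIS at every visit.
- All records: 100 × 3 = 300.
- From people who have received the intervention: 50 × 2 = 100.
- With no intervention to rate: controls 50 × 3 = 150, plus active arm at baseline 50, which gives 200.
- 200 / 300 = 67%.

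**The case against.** The strongest reply is that the documents do not plainly say that controls complete the QUIS. Section 2.4 describes self-reported data as collected at visits that form part of the intervention activities, and only the active arm has those. The statement that both arms follow Table 1 identically cannot hold for every row, because Table 1 also contains the stimulation activity. Table 3's caption is a single heading over a set of questionnaires from a project-wide protocol, and a condensed article may leave an exception for one instrument to the full protocol.

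This stands as far as the count goes. A reader might infer that 300 QUIS records are planned and that two thirds of them are empty. The documents state no such number, so 200 of 300 is only the result of the literal reading. It does not rescue the analysis. If the QUIS goes to the active arm alone, the two-condition model has no second condition and the baseline visit is still empty. Nor is this a detail left to the analysis plan, since section 2.7 itself assigns this outcome to this model.

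A second reply is that both arms use the remote speech application (section 2.4.7), so controls do have software to rate. That is correct, and it would be too strong to say that controls have no project software at all. But the application is an assessment tool. Section 2.7 and Table 3 both name satisfaction with the intervention, and nothing says that the application is the object rated.

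A third reply is that the year-2 ratings in the active arm are usable. This also stands. A reader might infer that only the 50 year-1 records count, but the 50 year-2 records have a defined object, recalled after use, and a year 1 to year 2 change within the active arm can be estimated.

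Finally, nothing in the article suggests that a between-arm satisfaction result would be presented as proof of acceptance. That risk is possible but not documented.

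**Conclusion.** The point holds. The stated analysis of satisfaction is misassigned: only 2 of 6 arm-by-visit cells have an intervention to rate, and from those cells no between-arm, change-from-baseline or group-by-time effect can be defined. This conclusion does not depend on who fills in the QUIS. It rests on two readings: that the models extended to satisfaction are the two-condition, three-visit models introduced just before, which is the natural sense of the text, and that the intervention means the stimulation programme. The figure of up to 200 of 300 records rests on the further assumption of full completion in both arms at all visits.

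The scope is one secondary outcome. The primary composites, quality of life and physical activity exist in both arms at every visit and are unaffected. A reader might infer a wider fault in the mixed-model plan, but the documents do not support that. It should be corrected, and it does not threaten the trial's main comparison.

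**What to change.** - In section 2.7, remove satisfaction from the outcomes analysed with the between-arm mixed models.
- State that the QUIS is reported in the active arm only, at visits after exposure: year 1, with year 2 optional and labelled as recall. Report it descriptively with confidence intervals.
- Add a footnote to Table 3 excluding the control arm and the baseline visit for the QUIS.

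A separate QUIS for each platform is not needed. Section 3 already accepts that the tools are delivered together and that their contributions are hard to separate, and ratings per platform would add to data collection.

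The cost is one sentence and one table footnote. No new data are needed. If the QUIS is at present given to controls or at baseline, the change also spares those participants a questionnaire that they cannot answer meaningfully.
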